## Discussion

4.

Food-Body-Mind study is a cluster RCT aimed to determine the effects on improving mental and cardiometabolic well-being in preschoolers and their caregivers from low-SES backgrounds. This study design builds on multiple pilot clinical trials demonstrating the feasibility and preliminary efficacy of mindfulness-based lifestyle interventions [26,33,52–54]. An initial 10-week lifestyle program tested with 69 preschooler-caregiver dyads showed feasibility and preliminary efficacy (Cohen’s *d* = −0.30 for reducing BMI z-score; *d* = 0.40 for increasing F/V intake; and *d* = 0.42 for increasing MVPA among preschoolers) [54]. From 2020 to 2024, three additional pilots (total *n* = 402 dyads) examined integrating mindfulness into the lifestyle program and delivering the caregiver component using a private website [33,52,53]. Results supported feasibility and suggested preliminary benefits for cardiometabolic health (decreased BMI, % body fat, blood pressure), healthy lifestyle behaviors (increased F/V intake, skin carotenoids), food insecurity, and the home environment. However, effects on dyadic mental health and long-tern sustained effects remain unknown. Therefore, conducting this fully powered clinical trial is necessary to evaluate the intervention’s short- and long-term sustained effects on mental and cardiometabolic health. This study will also identify theoretical mediators that can help explain the interconnections among food, body, and mind.

During implementation, we may face some challenges in recruiting and retaining families from low-SES backgrounds, variability in implementation fidelity across Head Start centers, missing or incomplete measures, and caregiver burden and limited access to resources. To mitigate these possible risks, we will 1) use multi-pronged recruitment through teachers and family-engagement staff, flexible scheduling, modest incentives, and frequent check-ins; 2) provide standardized training, manuals, and fidelity checklists with ongoing observation and feedback; 3) employ child-friendly assessment protocols, repeat or home-based data collection when needed, and robust missing-data methods (e.g., multiple imputation); 4) minimize caregiver burden through brief, virtual delivery, make-up sessions, and a resource booklet linking families to free or low-cost community options. Collectively, these contingency plans are designed to preserve implementation fidelity, reduce bias from missing data, and support equitable participation across diverse urban and rural settings.

The study has a few potential limitations including participants cannot be blinded to group assignment, and results may not be generalizable to preschoolers not attending daycare centers or other states in the U.S. Moreover, because the sample will comprise families from low-SES backgrounds, results may not generalize to children or families with different SES. Although language is not an inclusion/exclusion criterion, the current English-language data collection and intervention materials may limit participation for families who do not speak English, despite Head Start’s available interpretation services. This trial is not designed to modify the school environment or directly address family access to foods and activities; rather, it tests the effectiveness of a teacher-implemented child program with active caregiver engagement. Despite these possible limitations, the trial employs a rigorous cluster randomized design that accounts for random cluster effects and reduces contamination, with a large, community-based sample drawn from both urban and rural settings. Construct validity is strengthened through noninvasive biomarkers (hair cortisol, skin carotenoids, blood pressure) and objective measures (ActiGraph accelerometry, ShorrBoard^®^ stadiometry, bioelectrical impedance analysis). The intervention is theory-driven and integrates coordinated components across school, home, and the school-home connection, addressing multiple, mutually reinforcing contexts.

This trial will generate evidence on both immediate and sustained effects of a mindfulness-based lifestyle intervention on MEB and cardiometabolic health among preschoolers and their caregivers. By simultaneously engaging the school, home, and school-home connection, the study tests a multi-context approach that reflects real world conditions and may be more durable than single-setting programs. The findings can inform clinical and public health guidance for early prevention. If effective, Food-Body-Mind offers a feasible and developmentally appropriate model that Head Start and other early care and education systems could adopt to address MEB concerns alongside diet, PA, and metabolic domains that are rarely targeted together in early childhood. If effects are maintained at follow-up, the model would support policy arguments for investment in integrated, mindfulness-based lifestyle programs within early childhood systems.

Additionally, the study will contribute mechanistic insights. By examining theoretical mediators (e.g., caregiver mindfulness, coping, caregiver-child relationship, home environment) and objective/noninvasive markers (e.g., hair cortisol, skin carotenoids, blood pressure, accelerometry), the trial can clarify the food-body-mind linkage and identify leverage points for promoting well-being in early childhood. Following the trial, priorities include evaluating cost-effectiveness and pursuing longer-term follow-up into the elementary school years.

## Figures and Tables

**Fig. 1. F1:**
[figure not shown]
Flow diagram for the Food-Body-Mind study.

**Table 1 T1:** 16-week Food-Body-Mind intervention (three components: school-based, home-based, school-home connection).

Component	Dose	Theme, objectives, and description
*School-based* min*dfulness component for preschoolers*	20 min*/wk., 16 weeks*	*Mindful Eating – “Eat My ABCs ”* ***Objective:*** *Increase mindful eating knowledge and skills, expose children to healthy food options Each lesson structure:* ***Beginning:*** *Children are learning one fruit and one vegetable using 4 senses: see, feel, hear, smell*. ***Middle:*** *Children are practicing* min*dful eating to taste each fruit and vegetable*. ***End:*** *Reinforce the connection among food, body, and* mind: *benefits of healthy foods (*e.g.*, F/V) to our body (*e.g.*, help grow, become strong), mind (*e.g.*, be happy), and health (*e.g.*, not get sick)*.
	*20 min/wk., 16 weeks*	*Mindful Movement - “Walk My ABCs”* ** *Objective* ** *: Improve relaxation technique knowledge, skill, and physical activity Each lesson structure:* ***Beginning:*** *Warm up with jumping jacks and stretching and make body-*min*d connection (*e.g.*, connect movement to body and feelings)*. ***Middle:*** *Practice yoga poses (*e.g.*, airplane, butterfly, candle, down dog,* etc.*) and learn mindful breathing exercises with a breathing ball*. ***End:*** *Make the body-mind connection and reflect on the benefits of participating in physical activity and* mindful *movement* (e. g.*, help grow, be strong, stay healthy, sleep better, feel happy)*.
*Home-based mindfulness component for caregivers*	*1 flyer, 1 video, and 4 tasks/wk., 14 weeks*	*Social media-based program* ***Objective****: Foster a supportive virtual community among participating caregivers and provide parenting, health, and mindfulness information. One weekly electronically retrievable flyer and one short video modeling the daily* min*dful parenting practices at home by peer caregivers are shared each week*. *Weekly habit-formation tasks:* ***Create a healthy family****: post about a healthy meal made for their family, or a physical activity they helped child engage, or ways of practicing mindful eating and movement at home*. ***Raise a happy family****: post about a life management tip they used to manage life and stress, or a strategy used to improve parent-child relationship*. ***Leave a positive comment****: positively respond to one other person’s post to build a virtual supportive community*. ***Take a quiz:*** *take a short online quiz to reinforce information and strategies learned*.
	*3 texts/wk., 16 weeks* *1 text/wk., 12 months after intervention*	*Weekly motivational text messaging* ***Objective:*** *increase motivation to make healthy and mindful changes at home*. *A text message is sent on Monday, Wednesday, and Friday: 1) Monday messages will focus on parenting and family, 2) Wednesday messages on lifestyle changes and habit formation, and 3) Friday message on stress management and mindful practice. Weekly motivational text messages will continue during follow-up, once a week, on Monday*.
	*60 min/meeting, 3 meetings*	*Virtual group meetings at week 1, 8, 16* ***Objective:*** *strengthen child-parent relationship, connect caregivers for peer support, and enhance mindfulness practices at home. Each meeting will contain a 20-mintues yoga practice and discussion on mindful eating, mindful movement, and mindful parenting*.
*School-home connection*	*2 letters/wk., 16 weeks*	*Preschooler letters* ***Objective:*** *connect preschooler learning in daycare with caregiver practice at home, improve caregiver-preschooler relationship* *Each week at daycare, preschoolers will create two letters using stickers regarding the food and activities they tried, liked, and want to try at home*. *Caregivers are encouraged to discuss the letters with their preschooler and offer the food and activities at home. Caregivers will also be asked to answer two questions about the letters each week: (1) what foods listed in your child’s letter did you provide? (2) What activities listed in your child’s letter did your family try?*

**Table 2 T2:** Study outcomes and measures.

Variable	Measure and Description	# Items	Time	Reliability/Validity
**Aim 1 (Preschooler)**				
Behavioral health	Preschool and Kindergarten Behavior Scales-Second Edition (PKBS-2) [18] has two subscales: social skills and problem behaviors (**Primary outcome**).	76	12 min	**Internal consistency reliability** *a* = 0.75–0.97 [57] **Test-retest reliability** *r* = 0.58–0.87 **Validity** predicted autism spectrum disorders
Chronic stress	Hair cortisol concentration. Hair samples will be analyzed at Yale Child Study Center [34].	N/A	5 min	**Validity** *r* = 0.29–0.32 related to salivary cortisol [58]
Sadness	Sadness Parent Report Fixed Form [35]	7	2 min	**Internal consistency reliability** *a* = 0.77 **Convergent validity** = 0.38 [35]
Fear	Fear-Over Anxious Parent Report Fixed Form [35]	6	2 min	**Internal consistency reliability** *a* = 0.79 **Convergent validity** = 0.60 [35]
Anger	Anger Parent Report Fixed Form [35]	9	2 min	**Internal consistency reliability** *a* = 0.85 **Convergent validity** = 0.64 [35]
Positive affect	Positive Affect Parent Report Fixed Form [35]	9	2 min	**Internal consistency reliability** *a* = 0.92 **Convergent validity** = 0.95 [35]
BMI z-score	Calculated from height and weight using CDC growth charts [39] **Height:** Infant/Child/Adult ShorrBoard^®^ Measuring Board Stadiometer **Weight:** InBody 270 body composition analyzer	N/A	3 min	**Specificity** = 0.93 **Sensitivity** = 0.73 [59]
% Body fat	InBody 270 body composition analyzer applies bioelectric impedance technology to assess body composition including % body fat.	N/A	2 min	**Validity** highly correlated with the dual-energy X-ray absorptiometry method among children (*r* = 0.97) [38]
**Aim 2 (Caregiver)**				
BMI	Calculated using (weight *kg*/height *m*^*2*^) [60] Measures are the same as those used in preschoolers	N/A	3 min	**Specificity** = 0.97 **Sensitivity** = 0.42 [61]
% Body fat	InBody 270 body composition analyzer	N/A	2 min	**Validity** highly correlated with the dual-energy X-ray absorptiometry method among adults [62]
Blood pressure	SunTech CT40 Blood Pressure device	N/A	5 min	**Validity** achieved A/A grade of the British Hypertension Society protocol and reached the standard of the Association for the Advancement of Medical Instrumentation (AAMI)/the International Organization for Standardization (ISO) [40]
Stress	Perceived Stress Scale (PSS) [36]	10	2 min	**Internal consistency reliability** *α* = 0.74–0.91 **Test-retest reliability** *r* = 0.72–0.88 **Validity** *r* = 0.66–0.72 correlated with Hospital Anxiety and Depression Scale, *r* = 0.73 related to State-Trait Anxiety Inventory, *r* = 0.69 correlated with Post Traumatic Stress-Arousal Scale [63]
Anxiety & Depression	Patient Health Questionnaire ([PHQ]-4) [37]	4	1 min	**Validity** *r* = 0.80 with mental health **Construction validity** 2-factor structure [37]
**Aim 3 (Preschooler-Caregiver Dyads)**				
Physical activity (min/h)	7-day ActiGraph wGT3X-BT accelerometer **Cut-points for preschoolers:** sedentary activity (≤ 37 counts/15 s), light (38–419), moderate (420–841), & vigorous (≥842) [45] **Cut-points for caregivers:** light (0–2689 counts/60 s), moderate (2690–6166), & vigorous (≥ 6167) [64]	7-day	5 min	**Preschoolers:** **Reliability** = 0.69–0.84 [65] **Validity** *r* = 0.66 with observational system [66] **Caregivers:** **Reliability** ICC = 0.97–0.99 [67] **Validity** *r* = 0.81 with oxygen consumption [68]
F/V intake	Skin carotenoid level via Veggie Meter [42,69,70] 2-question survey adapted from the National Institute of Health Eating at America’s Table Study All-Day Screener	N/A	2 min	**Intra-individual variation of triple measurements** 6.8 % [43] **Validity** *r* = 0.81 related to serum carotenoid level [71], *r* = 0.48 related to self-reported F/V intake [43] Used in interventions to evaluate fruit/vegetable changes [44]
Caregiver-preschooler relationship	Child-Parent Relationship Scale (CPRS) [46,72] is a 5-point Likert scale with 2 subscales: conflict and closeness.	15	3 min	**Internal consistency reliability** *α* = 0.64–0.84 [46] **Construct Validity** 2-factor structure [73]
Caregiver mindfulness	Mindful Attention Awareness Scale [49] is a 6-point Likert scale to assess trait mindfulness.	15	3 min	**Reliability** 0.92 [74] **Construct validity** 1-factor structure [74]
Caregiver coping	Brief COPE [50] has 14 factors that can be grouped to 3 subscales: problem-focused coping, emotion-focused coping, and avoidant coping.	28	5 min	**Internal consistency reliability** *α* = 0.25–1.00 [75] **Test-retest reliability** = 0.32–1.00 [75] **Construct validity** 14-factor structure [50]
Home environment	Family Nutrition and Physical Activity Screening Tool [47]	20	4 min	**Internal consistency reliability** a = 0.75 **Validity** correlated with child BMI [47]
Household food insecurity	U.S. Household Food Security Survey Module [48]	19	4 min	**Sensitivity** = 32 % **Specificity** = 90 % [48]
Demographics	Socio-demographic questionnaire (e.g., age, sex, race, family income, education, marital, employment)	12	2 min	N/A

**Table 3 T3:** Schedule of assessment.

Assessments	T0 Recruitment	T1 Baseline (Month 0)	T2 Postintervention (Month 4)	T3 12-month follow-up (Month 16)
Parent Informed Consent	X			
Child Verbal Assent	X			
Teacher Consent		X		
Screening Survey	X			
Family Contact Information Survey	X		X	
Dyad Demographic Information	X			X
Teacher Demographic Information		X		

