## Aims

2.

The study has three specific aims: 1) Determine effects of the intervention on improving preschoolers’ behavioral (problem behaviors [primary outcome], social skills), mental (chronic stress by hair cortisol), emotional (sadness, fear, anger, positive affect), and anthropometric (body mass index [BMI] z-score, % body fat) health outcomes from baseline (0 month) to 4 months (immediate post-intervention) and to 16 months post-baseline (12-month follow-up) when compared to the control group; 2) Examine intervention effects on improving caregivers’ cardiometabolic (BMI, % body fat, blood pressure) and mental (stress, anxiety, depression) health from 0 to 4 months and to 16 months compared to the control; and (3) Explore the potential mediators (caregiver mindfulness, PA, F/V intake, caregiver-preschooler relationship, caregiver coping, home environment, and household food insecurity) of intervention effects.

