### Data collection and measures

3.6.

At each time point, data collection will include four components: 1) an online survey completed by caregivers and daycare teachers; 2) in-person data collection to measure dyads’ height, weight, % body fat, and skin carotenoid, as well as caregivers’ blood pressure; 3) ActiGraph (wGT3X-BT) accelerometer worn for 7 days to assess both preschoolers’ and caregivers’ PA (light PA, moderate to vigorous PA [MVPA]); and 4) hair sample collection to assess cortisol (as an indicator for chronic stress in the study) from a subgroup of preschoolers whose caregivers provided informed consent. Because this is a large-scale, community-based trial with young children and their caregivers from low-SES households, we intentionally selected noninvasive measures that provide reliable and valid assessments of mental and cardiometabolic health. We will not measure blood pressure in preschoolers due to inaccuracy from movement observed in our prior trial [33] and based on our pediatrician’s input indicating limited clinical significance of blood pressure screening in this age group in community settings. The study Data Manager and trained data collectors (blinded to group assignment) will be available by phone or in-person to answer questions. Table 2 depicts the measures used in this study and each measure’s reliability and validity. The schedule of assessment is demonstrated in Table 3.

**Preschoolers’ behavioral health** (problem behaviors and social skills) will be assessed using the Preschool and Kindergarten Behavior Scales-Second Edition [PKBS-2] [18]. This 76-item 4-point Likert scale contains two subscales: problem behaviors (42 items, *primary outcome*) and social skills (34 items). The four response choices for each item are never, rarely, sometimes, and often. Total raw scores will be calculated and converted to standard scores following the age-appropriate conversion tables [18]. The PKBS-2 will be completed by caregivers and teachers, with teacher-rated problem behaviors as the primary outcome.

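### Caregiver light physical activity is defined from 0 counts with no sedentary class, so as printed it is simply all non-MVPA time

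*Protocol article*

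**What the plan says.** Section 3.6 (Data collection and measures) names two intensity measures and applies them to both members of the dyad: "both preschoolers’ and caregivers’ PA (light PA, moderate to vigorous PA [MVPA"]). Table 2, in the Aim 3 block, gives the unit as "Physical activity (min/h") and lists two sets of cut-points in one cell.

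- Preschoolers: "sedentary activity (≤ 37 counts/15 s), light (38–419), moderate (420–841), & vigorous (≥842").
- Caregivers: "light (0–2689 counts/60 s), moderate (2690–6166"), with vigorous from 6167 counts upward.

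The preschooler set has four classes, the lowest being sedentary. The caregiver set has three, the lowest being light, and it starts at zero. No other part of the article gives a caregiver sedentary threshold or says that caregiver light PA is meant to include sedentary time.

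Physical activity enters the analysis through the third aim in Section 2: "Explore the potential mediators (caregiver mindfulness, PA, F/V intake" and further variables).

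**The concern.** Light activity normally means low-intensity movement as distinct from sitting still, and the preschooler row treats it that way. In the caregiver row, an hour spent motionless would be recorded as an hour of light activity. Because the device is worn through the waking day for a week (Section 3.6, paragraph on dyads' PA), sitting time will be in the record.

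At stake is whether caregiver light PA can serve as a measure in its own right. The caregiver component encourages mindful movement and includes yoga in each group meeting (Table 1), so a move from sitting to low-intensity activity is a plausible effect. A variable that pools the two states cannot show it. The same label would also mean different things for the child and for the adult in the published results.

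**Working it through.** The plan states no figure that depends on this point, so there is nothing to reproduce first. The check is whether the printed bands leave any room for sedentary time, and what follows if they do not.

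**Step 1. Coverage.** Inputs: the caregiver bands in Table 2 (0–2689, 2690–6166, and 6167 or more counts per 60 s). Every integer count from 0 to 20,000 falls into exactly one of the three bands, and the top band is open-ended. A count of 0 is classed as light. Under the preschooler cut-points, a count of 0 is classed as sedentary.

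**Step 2. Identity.** Take min/h as minutes per hour of wear. The three classes exhaust the hour:

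light + moderate + vigorous = 60, so light = 60 − MVPA.

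**Step 3. What the variable records.** With a separate sedentary class, light would be 60 − MVPA − sedentary. The documents give no caregiver MVPA or sedentary time, so the values below are assumptions for illustration (all min/h).

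| MVPA | Sedentary | Light as printed | Light with a sedentary class |
|---|---|---|---|
| 2 | 30 | 60 − 2 = 58 | 60 − 2 − 30 = 28 |
| 2 | 35 | 58 | 23 |
| 2 | 40 | 58 | 18 |
| 2 | 45 | 58 | 13 |

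The third column does not move with sitting time. A caregiver who goes from 35 to 30 min/h sedentary by moving gently gains 5 min/h of light activity (23 to 28). The printed definition records 58 both times, a change of 0.

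**Step 4. Direction of change.** Let MVPA rise from 1 to 3 min/h. The printed light PA falls from 59 to 57 whatever was replaced.

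- If MVPA replaced light movement (sedentary fixed at 35), true light goes from 24 to 22. The recorded fall of 2 is right.
- If MVPA replaced sitting (sedentary 35 to 33), true light is 60 − 1 − 35 = 24 before and 60 − 3 − 33 = 24 after. The recorded fall of 2 is an artefact.

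**Step 5. Consequence in a model.** Because light = 60 − MVPA, the correlation of the two is exactly −1, and a design matrix of intercept, light and MVPA has rank 2 instead of 3. An illustrative simulation with 400 caregivers gave −1.0 and rank 2. With an assumed sedentary class (mean 38, SD 5 min/h), the correlation was about −0.26 and the rank was 3. The −0.26 depends on those assumed values. The −1 depends only on the bands and the wear-time denominator.

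**The case against.** Several points can be made on the other side.

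- **The collinearity may never arise.** Section 2 lists the mediator only as PA, and Section 3.9.3 does not say which PA variable enters the structural equation model. A reader might infer that light PA and MVPA are to be entered together and that the Aim 3 model will fail. The article does not say so, and a singular model would be noticed at once. This stands: the collinearity is conditional on joint entry.
- **The sign is not always wrong.** A reader might infer that caregiver light PA runs in the wrong direction. As Step 4 shows, this is true only when MVPA replaces sitting. The accurate statement is that the variable cannot tell sitting from light movement.
- **No dyadic model is specified.** A reader might infer that the mismatch between child and adult definitions spoils an actor-partner analysis. That model appears in Section 3.4 as theory behind the intervention. The Aim 3 analysis text gives no actor-partner specification. What remains is an inconsistent label within one table cell.
- **The denominator is not spelled out.** Table 2 gives the unit without saying per hour of what. Wear time is the natural reading, and the exact identity needs it. On any other denominator, sitting is still scored as light activity.
- **The cited cut-point source may itself pool sedentary with light.** It is not available here. If it does, the numbers are faithfully reported and the fault lies in the label, because the band would be non-MVPA time and not a separate light-activity measure.
- **This is a condensed article, and scoring detail may sit in a fuller document.** That would excuse an absent threshold. It does not excuse a printed lower bound of 0, which is a definite rule that nothing else in the article corrects.

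**Conclusion.** The point holds as a defect in a stated definition. As printed, caregiver light PA is all time below the moderate cut-point. Per hour of wear it equals 60 − MVPA, adds nothing to MVPA, and shows no change when sitting gives way to light movement. Used alone as a mediator, it would return the MVPA result with the sign reversed. Entered beside MVPA, its path could not be estimated separately.

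The conclusion that sitting counts as light activity rests on the bands alone. The exact identity and the correlation of −1 also assume a wear-time denominator.

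The reach is limited to one exploratory Aim 3 mediator. It would be wrong to infer any threat to the trial's main conclusions: physical activity is not an Aim 1 or Aim 2 outcome, and the primary outcome, the power statement, preschooler PA and caregiver MVPA do not depend on this band. It should be corrected before the accelerometer data are scored for analysis, but it is not a fundamental flaw.

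**What to change.** In Table 2, add a caregiver sedentary cut-point on the same count metric as the moderate and vigorous cut-points, and start light PA above it. State the source of that cut-point, and state that min/h means minutes per hour of valid wear if that is what is intended.

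If no suitable cut-point is available, relabel the 0–2689 band as non-MVPA time, drop caregiver light PA from Section 3.6, and use caregiver MVPA alone as the caregiver PA mediator in Aim 3. Non-MVPA time should not be entered in a model alongside MVPA.

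The cost is a correction to one table cell, a matching phrase in Section 3.6, and re-scoring of the stored accelerometer files. No new data are needed. Settling the threshold before the mediation analysis also avoids choosing it in the light of the results.
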